## Abstract

**Background:**

Informing patients with cancer about the possible implications of prospective treatment is a crucial yet challenging task. Unfortunately, patients’ recall of medical information is generally poor and their information needs are not met. Effective information giving entails that oncologists help patients understand and recall the implications of their treatment, meanwhile fostering a trusting physician-patient relationship. Communication strategies that are often suggested to be effective are *structuring* and *tailoring* (cognition-oriented) but also are oncologists’ expressions of *caring* or empathy (affect-oriented).

**Objective:**

The aim of this study is to provide evidence concerning the pathways linking physician communication to (improved) consultation outcomes for patients. More specifically, the aim is to determine the effects of information *structuring* and information *tailoring*, combined with physician *caring*, on information recall, satisfaction with information, and trust in the physician (primary objective) and on symptom distress (secondary objective).

**Methods:**

A randomized controlled trial, systematically testing the effects of information *structuring* and information *tailoring*, each combined with *caring*, in 2 video-vignette experiments (2×2 and 2×2×2 design). Using an online survey platform, participants will be randomly allocated (blinded) to 1 of 12 conditions in which they are asked to view a video vignette (intervention) in which an oncologist discusses a treatment plan for malignant lymphoma with a patient. The independent variables of interest are systematically varied across conditions. The outcome measures are assessed in a survey, using validated instruments. Study participants are (former) patients with cancer and their relatives recruited via online panels and patient organizations. This protocol discusses the trial design, including the video-vignette design, intervention pretesting, and a pilot study.

**Results:**

Data collection has now been completed, and preliminary analyses will be available in Spring 2019. A total of 470 participants completed the first part of the survey and were randomized to receive the intervention.

**Conclusions:**

The results of the proposed trial will provide evidence concerning the pathways linking physician information, giving skills to (improved) consultation outcomes for patients.

**Trial Registration:**

Netherlands Trial Register NTR6153; https://www.trialregister.nl/trial/6022 (Archived by Webcite at http://www.webcitation.org/76xVV9xC8).

**International Registered Report Identifier (IRRID):**

DERR1-10.2196/12453

## Introduction

### Background

Informing patients with cancer about the possible implications of prospective treatment is a crucial yet challenging task. Cancer treatment plans are typically complex, and the effects on patients’ physical and psychological well-being can be severe. Although it is important that patients remember treatment information, research consistently shows that patients’ recall of medical information is poor [1-7]. Patients forget approximately 40% to 80% of the information that is provided by their oncologist [5,8-10].

Lack of information is not only potentially harmful but has also been cited as among the greatest causes of dissatisfaction in patients with cancer [1,6,11-13]. Patients mostly want information about treatment [14], particularly about symptoms and side effects, both in the short and long term [15-18]. Having information about symptoms and treatment may provide patients with a sense of control, reduce their anxiety and distress, and provide support coping with the physical and psychological demands of cancer treatment [18,19]. Additionally, by discussing current and future symptom experiences, physicians can influence patients’ expectations of symptoms and their ability to control symptoms [20]. These expectations may subsequently affect patients’ actual symptom experiences, either positively (placebo effect) or negatively (nocebo effect) [20,21].

Finally, providing comprehensive and understandable information that is congruent with patients’ needs is known to increase patients’ trust in the physician [22], which is associated with a higher tolerance for symptoms [21,23]. Indeed, patients with cancer who feel more able to cope with the disease and its treatment are better adjusted and experience greater quality of life than patients who feel less in control [24]. Therefore, effective information giving entails that oncologists help patients understand and recall the implications of their treatment, meanwhile fostering a trusting physician-patient relationship.

### Strategies of Effective Information Giving

Communication strategies to enhance information provision can be described as either cognition- or affect-oriented [25,26]. Cognition-oriented strategies are typically aimed at enhancing patient-related outcomes that are cognitive in nature, such as patients’ recall of information [27-31]. Two prominent cognition-oriented strategies are information *structuring* and *tailoring*. Affect-oriented strategies target patients’ emotions and include, for example, oncologists’ expressions of *caring* or empathy [9,31-35]. Owing to the inherent interplay between the cognition-oriented and affect-oriented aspects of information giving [36], these strategies should ideally be studied in conjunction.

#### Structuring

Structuring treatment information, that is, a clear organization of information provision during a consultation, is assumed to improve patients’ recall. Structure allows patients to systematically organize and store information in their working memory, such that it is easier to remember at a later moment [28,29]. Similar to the way in which newspaper articles or books are structured by means of, for example, (sub)titles and paragraph/chapter headings, physicians can use verbal structure *signals* to guide their patients through the information (also called the *book metaphor*) [28]. A total of 4 types of explicit verbal structure signals can be distinguished [37,38]: (1) Statements that set the agenda and announce key topics that will be dealt with in detail later (eg, “The most important issues to be discussed are...”); (2) Statements used to conclude or summarize the most important issues discussed (eg, “All in all, there are four main issues to be considered...”); (3) Ordinal or numeral signals that indicate elements of a series (eg, “first, second,...” and “in addition”); and (4) Statements expressing an opinion or a point of view (*“unfortunately”*; *“in my opinion”*) [37,38]. As early as in the 1970s, Ley et al found that the use of explicit structure signals in medical information can improve students’ memory [12]. Four decades later, Langewitz et al [28] demonstrated that providing verbal structure signals during discharge consults in emergency medicine significantly improved students’ recall. These results are yet to be replicated in clinical contexts.

#### Tailoring

Tailoring, that is, adjusting the (amount of) information to meet an individual patient’s information need, is proposed to be more effective than the provision of generic information [39,40]. People tend to pay more attention to information that they perceive as personally relevant, which leads to improved information processing and consequently better recall [40-42]. For patients with cancer, providing them with *less* information than they wish is known to cause dissatisfaction [16] and providing them with *more* information than they desire can also be harmful [43]. Consequently, a tailored approach, that is, congruence between the patients’ information need and physician's information provision, is generally advocated [40,41,43-46].

#### Caring

Caring refers to a communication style in which the physician displays behaviors of empathy for and affective engagement with the patient [9,47,48,49], thereby potentially reducing patients’ emotional distress [9,32,48] and enhancing patients’ memory of information [49,50]. A sense of a caring relationship with the physician has been shown to increase patients’ satisfaction with the provided information [34]. Other studies demonstrate that patients’ trust in their physician reduces the need to subsequently seek detailed information [44,51]. Moreover, research suggests that physicians can help alleviate symptom distress by affective communication, rather than by information giving alone [21,52].

The effectiveness of the aforementioned cognitive (ie, structuring and tailoring) and affective (ie, caring) strategies may differ, depending on patients’ individual characteristics known to affect information processing, such as their age [5], their degree of anxiety [35] or coping style [53], or their medical history.

### Research Objectives

The randomized controlled trial described in this study protocol aims to provide evidence concerning the pathways linking physician communication to (improved) consultation outcomes for patients. More specifically, it seeks to determine the effects of information *structuring* (experiment 1) and information *tailoring* (experiment 2), combined with physician *caring*, on information recall, satisfaction with information, and trust in the physician (primary objective). Additionally, it aims to determine the effects of these independent variables on expected symptom distress (secondary objective). The planned trial consists of a single study in which 2—analytically distinct—subexperiments can be identified—each with specific objectives related to the independent variables.

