### Hypotheses and Research Questions

The hypotheses and research questions are as follows (see Figure 1):

Experiment 1: StructuringH1: Information *structuring* positively affects patients’ recall of treatment information.Experiment 2: TailoringH2: Information *tailoring* positively affects patients’ recall of treatment information.Experiments 1 and 2: CaringH3: Oncologists’ expressions of *caring* positively affect patients’ recall of, and satisfaction with, treatment information and their trust in the oncologist.RQ1: Is there an interaction effect of information *structuring* or *tailoring* and oncologists’ expressions of *caring*?RQ2: Do patients’ recall of, and satisfaction with, treatment information and their trust in the oncologist affect patients’ expected symptom distress?RQ3: Do patient characteristics, including sociodemographics (eg, gender, age, and health literacy), medical history (eg, type and year of diagnosis and treatment), and personality traits (eg, coping style and trait anxiety), moderate the hypothesized relationships?

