### Analysis

Data will be cleaned in a stepwise procedure [76], including the identification of missing values because of dropout, standardization and normalization of data, and outlier analysis. Data will subsequently be analyzed using IBM SPSS statistical package. In the first step, it will be determined whether the experimental groups, within each of the 2 subexperiments of the trial, are indeed comparable in terms of participant characteristics, such as sociodemographics, personality traits, and disease history. If differences are found, these will be controlled for in subsequent analyses. Then, for each of the 2 experiments, one-way analysis of variance or covariance (when aspects need to be controlled for) will be conducted to test the effects of information structuring, information tailoring, and caring on information recall, satisfaction, and trust (H1, H2, and H3, respectively). Additionally, the interaction effect between caring and information structuring as well as tailoring will be added to these models (RQ1). It will be investigated to what extent patient characteristics moderate the hypothesized relationships (RQ3). If necessary, because of violations of the assumption of homogeneity of variance, Welch F statistic will be employed. Posthoc comparisons, using Bonferroni or Games-Howell, will be used as applicable, to create a better understanding of between-group differences. Finally, linear regression analyses will be used to assess possible relationships of information recall, satisfaction, and trust with expected symptom distress (RQ2). Significance levels are determined at *P*<.05.

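### The secondary objective, the effect of structuring, tailoring and caring on expected symptom distress, has no matching question or analysis; distress is analysed only by regression on non-randomised post-video variables

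*Protocol article*

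**What the plan says.** Research Objectives (Protocol article, Introduction) gives the secondary objective: "Additionally, it aims to determine the effects of these independent variables on expected symptom distress (secondary objective". The Objective paragraph of the Abstract agrees. It lists the effects of structuring and tailoring, combined with caring, on recall, satisfaction and trust as the "primary objective) and on symptom distress (secondary objective".

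Under Hypotheses and Research Questions, distress is named once, in RQ2, which asks whether recall, satisfaction with "treatment information and their trust in the oncologist affect patients’ expected symptom distress".

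The Analysis section assigns an analysis to each question:

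- ANOVA or ANCOVA, to "test the effects of information structuring, information tailoring, and caring on information recall, satisfaction, and trust (H1, H2, and H3, respectively".
- Interactions: "Additionally, the interaction effect between caring and information structuring as well as tailoring will be added to these models (RQ1".
- Distress: "linear regression analyses will be used to assess possible relationships of information recall, satisfaction, and trust with expected symptom distress (RQ2".

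The same section says that participant characteristics found to differ between the experimental groups will be controlled for in later analyses.

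**The concern.** The objective concerns an effect of randomised factors, but the only analysis with distress as outcome contains no randomised factor. Its predictors are recall, satisfaction and trust, which participants report after the video. They are outcomes of the experiment and share causes with distress. A generally anxious participant may well trust the oncologist less and also expect more distress.

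Two things are at stake. First, a stated objective would get no randomised estimate, although randomisation provides one directly. Second, RQ2 asks whether these variables *affect* distress, and the Implications section promises to clarify how physician skills relate to recall, satisfaction, trust and ultimately symptom distress. Without the factor-on-distress comparison, that last step would rest on associations alone.

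**Working it through.** **1. Objective against analysis.**

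| Outcome | Effect of the factors an objective? | Hypothesis or question on that effect | Analysis with the factors |
|---|---|---|---|
| Recall, satisfaction, trust | Yes, primary | H1 to H3, RQ1 | ANOVA/ANCOVA with interactions |
| Expected symptom distress | Yes, secondary | None | None |

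The independent variables in the objective cannot be recall, satisfaction and trust. The Experimental Manipulations section uses the term for structuring, tailoring and caring, and the Sample Size section calls recall, satisfaction and trust the dependent variables. The RQ1 interactions go into the same ANOVA models, so they do not bring distress in.

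**2. The plan's own sample size.** Inputs from Sample Size: alpha .05, power .80, effect sizes .10 to .25 (read here as Cohen's f, an assumption), N = 180 and 240. For a one-way omnibus F test, the noncentrality is λ = N·f².

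- Structuring, 4 groups, f = .25: λ = 180 × .0625 = 11.25, df 3 and 176, power .804. The smallest sufficient N is 179, or 180 with equal groups.
- Tailoring, 8 groups, f = .25: λ = 240 × .0625 = 15.0, df 7 and 232, power .807. The smallest sufficient N is 237, or 240 with equal groups.

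The stated 180 + 240 = 420 is reproduced at f = .25. Distress is not among the outcomes it was sized for.

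**3. Power of the missing test at the planned N.** A main effect has 1 df. Tailoring as match against mismatch is also a 1-df contrast.

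| | N = 180 | N = 240 |
|---|---|---|
| f = .25 | λ = 11.25, power .916 | λ = 15.0, power .971 |
| f = .10 | λ = 1.8, power .266 | λ = 2.4, power .339 |

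**4. Why the regression is no substitute.** Assumptions, none from the document: trait anxiety correlates −r with trust and +r with distress, and trust has no effect on distress. Trust and distress then correlate at −r², that is −.04, −.09 and −.16 for r = .2, .3 and .4. With z = atanh(r²)·√(N − 3), the two-sided rejection rate is Φ(z − 1.96) + Φ(−z − 1.96).

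| N | r = .2 | r = .3 | r = .4 |
|---|---|---|---|
| 180 | z = 0.532: 8.3% | z = 1.201: 22.5% | z = 2.147: 57.4% |
| 240 | z = 0.616: 9.5% | z = 1.389: 28.5% | z = 2.485: 70.0% |
| 420, pooled | z = 0.817: 12.9% | z = 1.843: 45.3% | z = 3.296: 90.9% |

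Simulation of the same set-up agrees to about one percentage point (8%/23%/57% at N = 180; 9%/28%/70% at N = 240). A separate simulation at N = 180, with r = .2, .3 and .5 and a factor that shifts trust by 0.5 SD, gave rejection rates of 7%, 22% and 92% for the regression. The randomised contrast on distress stayed at 4.5% to 4.7%.

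**The case against.** Several points on the other side stand, and they limit how far the concern reaches.

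- A reader might infer that the RQ2 regression has no adjustment at all. The document does not support that, because its rule on group differences can reach later analyses, including this one. But the rule is triggered by chance imbalance between arms, not by confounding of trust with distress, so trait anxiety or coping style would enter only by chance. RQ3 treats such traits as moderators, which is not confounder adjustment.
- A reader might infer that the randomised evidence is wasted generally. It is used for H1 to H3 and RQ1; the gap is distress only.
- A reader might infer that the plan declares the regression to be its secondary-objective analysis. It labels it RQ2 only and speaks there of possible relationships. The causal verb is in the wording of RQ2 itself.
- A reader might take the pooled N = 420 rates as the size of the problem. Research Objectives calls the two subexperiments analytically distinct, and they are sized separately, so the 180 and 240 rows are the fairer ones. The illustration also uses one predictor where the plan names three.
- Figure 1 is not available to this review and may draw a direct path from factors to distress. A path in a figure would still not supply the missing model.

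Brevity does not explain the gap. The article pairs each analysis with its hypothesis or question, and distress is paired only with RQ2.

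**Conclusion.** The contradiction between objective and analysis holds on the text alone and needs no assumption. Followed as written, the trial produces no randomised estimate of the effect of structuring, tailoring or caring on expected symptom distress.

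The rejection rates in the working rest on assumed correlations and a single predictor. They show that the RQ2 regression can mislead, by a little at r = .2 and badly at r = .4, but they do not measure the missing test. Severity is should-fix: the objective is secondary, the sample was not sized for it, and the primary analyses are unaffected.

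**What to change.** In each experiment, add expected symptom distress as an outcome of the same factorial ANOVA/ANCOVA used for H1 to H3, and label this the secondary-objective analysis. Define the scores beforehand, for example one each for probability, severity and controllability across the four complaints. Report estimates with confidence intervals, since power is good at f = .25 but poor at f = .10.

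Keep RQ2 as an association or mediation analysis. Include the randomised factors and prespecified baseline covariates already collected, such as trait anxiety and coping style; the exact set is the investigators' choice. In RQ2, replace *affect* with *are associated with*.

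Rewording the objective to match RQ2 would also remove the contradiction, but it would give up the randomised comparison.

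The cost is some extra secondary tests and no new data. With tailoring coded as match against mismatch, each experiment has two main effects and one interaction, so three scores in two experiments give 3 × 3 × 2 = 18 tests, to be read as secondary. The Results section reports data collection complete with first analyses still to come, so the addition should be dated and described as made after data collection.

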### Hypotheses and Research Questions

The hypotheses and research questions are as follows (see Figure 1):

Experiment 1: StructuringH1: Information *structuring* positively affects patients’ recall of treatment information.Experiment 2: TailoringH2: Information *tailoring* positively affects patients’ recall of treatment information.Experiments 1 and 2: CaringH3: Oncologists’ expressions of *caring* positively affect patients’ recall of, and satisfaction with, treatment information and their trust in the oncologist.RQ1: Is there an interaction effect of information *structuring* or *tailoring* and oncologists’ expressions of *caring*?RQ2: Do patients’ recall of, and satisfaction with, treatment information and their trust in the oncologist affect patients’ expected symptom distress?RQ3: Do patient characteristics, including sociodemographics (eg, gender, age, and health literacy), medical history (eg, type and year of diagnosis and treatment), and personality traits (eg, coping style and trait anxiety), moderate the hypothesized relationships?

**Figure 1 figure1:**
[figure not shown]
Hypotheses and research questions.

## Methods

### Trial Design

The trial employs a between-subjects single-message factorial design in which the independent variables of interest are systematically manipulated. This is done using the video vignette methodology. In experiment 1, hematologists’ information structuring and expressions of caring are varied in a 2 (standard versus enhanced structuring) × 2 (standard versus enhanced caring) design. In experiment 2, hematologists’ information tailoring and expressions of caring are varied in a 2 (high versus low need for information) × 2 (high versus low amount of information provided) × 2 (standard versus enhanced caring) design. This results in 12 experimental conditions, or interventions, across the trial (see Tables 1 and 2).

**Table 1 table1:** Experiment 1: Manipulation of provider information structuring and caring (2×2 design).

Manipulations	Standard of care	Caring
Standard of care	Standard of care	Enhanced caring
Structuring	Enhanced structuring	Enhanced caring and structuring

**Table 2 table2:** Experiment 2: Manipulation of provider caring and information tailoring in a match/mismatch design (2×2×2 design).

Manipulations		Provider			
		Enhanced caring		No caring	
		Additional information provision	No additional information provision	Additional information provision	No additional information provision
**Patient**					
	High information need	Tailoring match; (++^a^)	Tailoring mismatch; (+ −^b^)	Tailoring match; (++)	Tailoring mismatch; (+ −)
	Low information need	Tailoring mismatch; (− +^c^)	Tailoring match; (− −^d^)	Tailoring mismatch; (− +)	Tailoring match; (− −)

^a^Patient with high information need receiving additional information provision.

^b^Patient with high information need yet not receiving additional information.

^c^Patient with low information need nevertheless receiving additional information.

^d^Patient with low information need not receiving additional information.

### Study Setting

The trial is set within the specific context of hematology and the treatment of malignant lymphoma (diffuse large B-cell lymphoma [DLBCL]). Treatment information, including information about likely symptoms, is particularly important in this context because treatments are highly unpleasant and require patients’ commitment and adherence in the face of these demands [36]. The trial is conducted in the Netherlands. This study has been evaluated by the medical ethical committee of the Academic Medical Center. The institutional ethics committee has determined that the study is exempt from the need for review according to the Dutch regulations for research involving human subjects (W16_054 # 16.069, date: February 2016).

